### Intervention:

***Visit 2 (Week 2):*** First dose of oral or IV iron will be administered, and adverse effects will be monitored.

***Visit 3 (Week 6):*** Second doses will be administered; compliance and adverse effects will be monitored.

***Visit 4 (Week 10):*** Third doses will be administered; compliance and adverse effects will again be monitored.

***Post-Intervention Data Collection (Visit 5, Week 16):*** The participants from all three study groups will be contacted. Blood samples have to be collected to measure the efficacy of iron treatment on ferritin levels. The symptoms severity levels will also be recorded again to assess the effectiveness of the intervention.

***Compliance:*** To enhance compliance, participants in Group-B will receive daily reminder messages or calls regarding their supplementation regimen.

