**Methods::**

We will choose a multicenter, multi-arm randomized controlled trial with a parallel assignment interventional model. About three hundred participants (n=300) aged 18-45 with hypoferritinemia without anemia and no comorbidities will be recruited. Participants will be randomized into three groups of one hundred each: Group-A will receive oral iron supplements (Iron III Hydroxide Polymaltose Complex, 100 mg elemental iron) one tablet per day for three months; Group-B will receive intravenous iron (Ferric carboxymaltose, one dose per month for three months); Group-C will receive no treatment. All groups will be followed for four months.

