
### Research Objectives:

To compare the effects of` oral iron (Iron III Hydroxide Polymaltose Complex eq. to Elemental Iron, 100 mg per day for three months) supplementation (Group-A) versus Intravenous (IV) iron (Ferric carboxymaltose 500 mg, three doses for three months) (Group-B) versus no treatment (Group-C) on serum ferritin level, four months post-intervention.To evaluate the change in the severity of clinical indicators of Hypoferritinemia without Anemia between Group A, B and C, four months post-intervention.

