### Intervention:

***Group-A (n=100):*** Participants will receive oral iron supplementation (Iron III Hydroxide Polymaltose Complex, 100 mg) daily for three months, with compliance monitored through follow-up calls. Blood samples will be collected at the end of treatment period of four months.

***Group-B (n=100):*** Participants will receive IV iron supplementation (Ferric Carboxymaltose, 500 mg) once a month for three months. Blood samples will be collected at the end of treatment period of four months.

***Group-C (n=100):*** Participants will receive no treatment for three months. Blood samples will be collected at the end of treatment period of four months.

Randomized Controlled Trial Steps

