### Outcome Measures:

### Primary Outcome:

The primary outcome will be change in serum ferritin levels from baseline to Visit five. This will be measured by analyzing the difference in the treatment outcome of oral iron supplementation Group-A, intravenous iron supplementation Group-B and no treatment Group-C, four months post-intervention. A 5ml blood sample for measuring serum ferritin levels will be drawn by the phlebotomist at visit five to access the change in the value of serum ferritin from baseline.

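### The daily compliance reminders are assigned to Group-B, the once-a-month IV arm, and not to the daily-tablet arm; probably a label slip, but it would tilt oral v IV if followed

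*Protocol article*

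**What the plan says.** The arm labels are consistent wherever the treatments are described.

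- **Group-A (oral).** The Research Objectives give oral iron as "100 mg per day for three months) supplementation (Group-A) versus Intravenous (IV) iron", so the daily regimen belongs to Group-A. The arm description under Intervention has the product taken "daily for three months, with compliance monitored through follow-up calls".
- **Group-B (intravenous).** The Abstract says "Group-B will receive intravenous iron (Ferric carboxymaltose, one dose per month for three months". The arm description agrees: "Participants will receive IV iron supplementation (Ferric Carboxymaltose, 500 mg) once a month for three months".
- **Group-C.** No treatment.

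The visit-by-visit part of the Intervention section places the doses at Visits 2, 3 and 4 (weeks 2, 6 and 10). For Visit 3 it adds: "Second doses will be administered; compliance and adverse effects will be monitored". Visit 4 has the same provision, and neither is limited to one arm.

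The Compliance paragraph that closes this part then says that "participants in Group-B will receive daily reminder messages or calls regarding their supplementation regimen". No section gives Group-A daily reminders, and none explains why a monthly infusion would need them.

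**The concern.** A daily reminder helps where a participant has something to do every day. In this trial that is Group-A alone. In Group-B the doses are given at visits a month apart, so a daily message can at most support attendance at those visits.

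Two consequences follow if site staff apply the sentence literally.

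- **Primary outcome.** The article states that "The primary outcome will be change in serum ferritin levels from baseline to Visit five". Group-A is the only arm whose iron exposure depends on self-taken doses. Without the daily aid, missed tablets could lower its ferritin gain. The oral v IV contrast would then mix route of administration with a difference in adherence support.
- **Secondary outcome.** Symptom severity comes from a history taken by a research assistant. Frequent contact in one arm only could influence what women report, in B v A and in B v C.

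Both would tend to favour IV, which is the direction of the hypothesis in the Sample Size section.

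**Working it through.** The plan gives no figure on this point to reproduce, and the point does not depend on the sample size, alpha or power. The check is a comparison of sections, plus a count.

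**Step 1: arm by arm, as written**

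| | Group-A | Group-B | Group-C |
|---|---|---|---|
| Regimen (Abstract, Research Objectives, arm descriptions) | one tablet a day, three months | one infusion a month, three months | none |
| Where doses are taken | by the participant, between visits | at Visits 2, 3 and 4 | not applicable |
| Daily reminders (Compliance paragraph) | none stated | yes | none stated |
| Follow-up calls on compliance (arm descriptions) | yes, frequency not stated | none stated | none stated |
| Compliance checks at Visits 3 and 4 | yes | yes | not excluded by the text |

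That infusions are given at the visits is read from the visit descriptions and from Table-I, which has study medication given at Visits 2, 3 and 4.

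**Step 2: reminders against dosing occasions**

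- Three months taken as 12 to 13 weeks: 12 × 7 = 84 days to 13 × 7 = 91 days.
- Group-B as written: 84 to 91 daily reminders for 3 infusions, or 84/3 = 28 to 91/3 ≈ 30 reminders per dose.
- Group-A as written: 84 to 91 self-taken tablets, with no daily reminder stated.

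These are counts of reminders. The article allows messages or calls, so they are not counts of conversations with staff.

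**Step 3: which outcome each mechanism can reach**

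- Missed tablets in Group-A can reach serum ferritin directly, and symptoms through it.
- Extra contact in Group-B can plausibly reach reported symptoms. It has no evident route to a laboratory ferritin value.

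**Step 4: can the effect be sized?** That would need oral adherence with and without reminders, the relation of tablets taken to ferritin gain, and the expected ferritin difference with its SD. The article gives none of these.

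**The case against.** The strongest reply is that this is a slip of one letter and not a design decision. A daily reminder about supplementation fits only the tablet arm, and the authors may well have meant Group-A. That is the likelier reading. It makes the bias conditional on the sentence being followed, but it does not remove the need to correct a working instruction that names an arm.

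Four stronger readings are tempting and are not supported.

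- **That the sections contradict each other outright.** They do not. Group-A can have follow-up calls while Group-B has reminders; both instructions can be carried out. The fault is an assignment that does not fit the arm's regimen.
- **That adherence in Group-A is unsupported.** It is not. Group-A has the follow-up calls and the checks at Visits 3 and 4. These lessen the imbalance, but monitoring is not a daily prompt and the frequency of the calls is not stated.
- **That the contact effect biases the primary outcome.** The documents give no route from messages to a laboratory ferritin value. Even for symptoms, the reminders are not the only source of difference: no placebo is described, so women can be expected to know whether they receive tablets, infusions or nothing.
- **That the loss in the oral effect can be quantified.** A reader might assume 60–80% adherence without reminders, 90% with them, and ferritin gain proportional to tablets taken, which gives 1 − 0.8/0.9 = 11% to 1 − 0.6/0.9 = 33%. Every input there is an assumption with no basis in the article, so the result should carry no weight.

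**Conclusion.** The point holds as an error in the text with a conditional consequence. The Compliance paragraph gives a daily adherence aid to the arm without a daily regimen, at odds with three consistent descriptions of the arms. Followed literally, it would withhold the aid from the only arm with self-taken daily doses. The ferritin comparison of oral with IV iron could then shift towards IV through missed tablets, and symptom reports in Group-B could shift through contact.

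The direction rests on two assumptions: that the sentence is applied as written, and that daily reminders would improve tablet-taking beyond what the calls and visit checks achieve. The size is unknown and cannot be derived from the article. If the label is a slip and the sites already send the reminders to Group-A, the oral v IV ferritin comparison is not harmed in this way and only the wording needs correcting.

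**What to change.** Reconcile the arm label in the Compliance paragraph with the regimens in the Abstract, the Research Objectives and the arm descriptions, so that the daily reminder is tied to the arm with the daily regimen. Confirm that site instructions carry the same label.

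This will not equalise contact: the daily messages would then sit in Group-A alone. State that remaining difference between the arms as a limitation when symptom scores are interpreted. Equal contact in all three arms would be a separate design choice and is not needed to correct this error.

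The cost is one corrected label and one sentence on interpretation. No treatment, visit, outcome or sample size changes. It should be done before reminders are sent, because an imbalance that has already occurred cannot be undone in the analysis.

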**Fig-1 F1:**
[figure not shown]
Framework of Randomized controlled trial Framework for randomized controlled trial is illustrated in Fig. 1 (also attached separately).

### Outcome Measures:

### Primary Outcome:

The primary outcome will be change in serum ferritin levels from baseline to Visit five. This will be measured by analyzing the difference in the treatment outcome of oral iron supplementation Group-A, intravenous iron supplementation Group-B and no treatment Group-C, four months post-intervention. A 5ml blood sample for measuring serum ferritin levels will be drawn by the phlebotomist at visit five to access the change in the value of serum ferritin from baseline.

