## Abstract

**Background & Objectives::**

Hypoferritinemia without anemia (HWA) is an under-recognized public health concern. Early identification and targeted treatment of HWA can prevent unnecessary medication use and potential drug abuse. This study aims to establish clearer guidelines for recognizing and managing HWA, improving patient’s outcome. The study objectives will be to compare the treatment efficacy of oral and IV iron on patients with HWA and to check the severity of clinical indicators of HWA post treatment among reproductive age women.

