## INTRODUCTION

Iron Deficiency Anemia (IDA) is a widely recognized condition affecting over one billion people globally, however Hypoferritinemia without Anemia (HWA) is estimated to be at least twice as prevalent.^1^ In clinical practice, hypoferritinemia without anemia can be ascertained in adults (ages 15 to 45) when hemoglobin levels are normal (≥12 g/dl) but ferritin levels dip below 30 ng/ml.^1^ According to a study conducted on iron treatment among healthy males and females aged >15 years, a ferritin cut-off of 30 ng/ml is recommended.^2^,^3^ Another study on iron deficiency without anemia shows that the serum ferritin concentration (cut off <30 ng/ml) is the most specific test used for the identification of iron deficiency.^4^ The common symptoms of HWA include fatigue, poor work productivity, cognitive difficulties, hair loss, palpitations, sore tongue, restless leg syndrome, and poor skin, hair, and nail health.^5^,^6^ Despite its prevalence, HWA is frequently overlooked by clinicians, likely due to suboptimal screening practices and reliance on hemoglobin levels alone for diagnosis.^7^ Some patients with HWA may have had profound symptoms for many years while their blood count has been normal throughout.^8^ The normal Complete Blood Count (CBC) results make HWA a hidden disease with a lack in exact underlying cause.^9^ Similar symptoms are experienced by patients suffering from iron deficiency anemia (IDA) and HWA however, the sufferers of the latter condition suffer from wrong or no diagnosis as compared to IDA which is easily diagnosed through complete blood count (CBC).^9^ Because the symptoms and signs of HWA are not specific, which may occur in other physiological or psychiatric conditions, patients with HWA are either suggested no tests or can result in expensive tests for heart or renal failure as a result of complication of chronic iron deficiency,^5^,^10^,^11^ which may be avoidable if simple, cost-effective tests such as serum ferritin, folic acid, and vitamin B12 are conducted on time.^12^,^13^ HWA presents a diagnostic challenge as it mimics the symptoms of IDA, yet remains undiagnosed due to normal hemoglobin and CBC results.^5^ Clinicians generally recommend iron assessments when there has been evidence of anemia, resulting in undetected HWA.^4^ The clinician typically does not make an effort to identify the underlying cause of the symptoms, with the exception of chronic disease study, and instead prescribes symptomatic treatment, which might lead to drug misuse or overmedication e.g., pain killers, anti- depressants or anti-anxiety drugs, sleeping tablets and overdose of multivitamins.^14^-^15^ This study aims to bring attention to the under-recognition of HWA, advocating for better diagnostic protocols and targeted treatments to the clinicians. This study has to be carried out because not only it will help patients determine the category of HWA, but it will also assist them to obtain specific treatment, reducing their risk of drug misuse and overmedication. To date, no study on HWA has been conducted in Pakistan on non-pregnant women, highlighting the need for research in this population.

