### Sample Size:

The sample size will be calculated under the hypothesis that intravenous (IV) treatment will more effectively alleviate symptom scores compared to oral or no intervention after four months. Based on a 41.7% prevalence of HWA^16^ and an anticipated 45% reduction in prevalence post-intervention, a sample size of ninety-six patients per group is required, with a 5% inflation for loss to follow-up. Therefore, one hundred patients will be recruited in each of the three groups, totaling three hundred participants.

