### Secondary Outcome:

The secondary outcome will be change in severity of clinical symptoms of hypoferritinemia without anemia. The secondary outcome will be measured by analyzing the difference in the severity of clinical symptoms of hypoferritinemia without anemia in oral iron supplementation Group-A, intravenous iron supplement Group-B and no treatment Group-C, four months post-intervention. A detailed history of clinical symptoms of hypoferritinemia without anemia will be taken by the research assistant in order to assess the severity of clinical symptoms post intervention.

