### Statistical Analysis:

SPSS version 24 will be used for data analysis. Descriptive and inferential statistics will be used. Comparisons will be made using independent sample t-tests, paired sample t-tests, Wilcoxon rank tests, Friedman tests, and ANOVA, as appropriate based on normality assessed by the Shapiro-Wilk test.

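### The trial is sized on a fall in HWA prevalence, but no planned outcome or test covers the proportion of women no longer below ferritin 30 ng/ml

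*Protocol article*

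**What the plan says.** The Introduction defines HWA in adults by two laboratory values: "hemoglobin levels are normal (≥12 g/dl) but ferritin levels dip below 30 ng/ml". The Inclusion Criteria use the same two limits, so every randomised woman starts below 30 ng/ml. The Abstract gives the practical purpose: "This study aims to establish clearer guidelines for recognizing and managing HWA".

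The Sample Size section states its basis as follows: "Based on a 41.7% prevalence of HWA^16^ and an anticipated 45% reduction in prevalence post-intervention". From this it reaches 96 per group, and 100 per group are to be recruited. The same section words its hypothesis in terms of symptom scores.

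Under Outcome Measures there is one primary outcome, "The primary outcome will be change in serum ferritin levels from baseline to Visit five", and one secondary outcome, "The secondary outcome will be change in severity of clinical symptoms of hypoferritinemia without anemia". Ferritin is measured in each woman at the end: "A 5ml blood sample for measuring serum ferritin levels will be drawn by the phlebotomist at visit five". The Statistical Analysis section lists the methods: "Comparisons will be made using independent sample t-tests, paired sample t-tests, Wilcoxon rank tests, Friedman tests, and ANOVA", chosen according to a normality test. It lists no method for comparing proportions.

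**The concern.** HWA is a threshold condition, and the sample size treats benefit as fewer women having it. That benefit then drops out of the plan: neither outcome records whether a woman is still below 30 ng/ml, and no listed test would compare arms on it.

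Two things are at stake. First, a comparison of ferritin change between oral and intravenous iron can show which arm rises more without showing how many women in each arm are no longer hypoferritinemic. The Discussion presents the choice between oral and intravenous iron as contested, and that count bears directly on it. Second, if the proportion is produced after the data are seen, its cut-off, its denominator and its handling of missing samples are open to choice, and it carries less weight than a planned result.

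**Working it through.** **1. The plan's own figure.** Inputs from Sample Size: 41.7% and a 45% reduction. An absolute fall of 45 points from 41.7% is impossible, so the reduction is read as relative: p1 = 0.417, p2 = 0.417 × 0.55 = 0.229, difference 0.188, average 0.323. The article gives no alpha, sidedness or power. Two-sided 5% and 80% power are assumed (z = 1.960 and 0.842).

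- Pooled: n = [1.960 × √(2 × 0.323 × 0.677) + 0.842 × √(0.417 × 0.583 + 0.229 × 0.771)]² / 0.188² = 96.3 per group.
- Unpooled: n = (1.960 + 0.842)² × (0.417 × 0.583 + 0.229 × 0.771) / 0.188² = 93.6 per group.

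The stated 96 is therefore what a comparison of two proportions gives. One-sided 5% gives 76 and 90% power gives 129, so the assumed settings are the ones that fit. The match is not proof of method: a single-proportion precision formula, 1.96² × 0.25 / 0.10² = 96.04, lands on the same number. Either way the basis is a proportion, not a change in ferritin level or a symptom score.

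**2. Sizing basis against outcomes.**

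| Section | Quantity |
|---|---|
| Sample Size, hypothesis | symptom scores |
| Sample Size, figures | prevalence of HWA (proportion) |
| Primary Outcome | change in ferritin (continuous) |
| Secondary Outcome | change in symptom severity |
| Statistical Analysis | t-tests, rank tests, Friedman, ANOVA |

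The proportion appears only in the sizing. In addition, 41.7% cannot be the starting rate in this trial, because entry requires ferritin below 30 and the rate at baseline is 100%.

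**3. Does a change in level determine the proportion?** The documents give no ferritin distribution, so this is an illustration. Assume Visit 5 ferritin is log-normal with arithmetic mean m and log SD s. The median is m × exp(−s²/2), and P(≥30) = 1 − Φ[(ln 30 − ln median)/s].

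| s | m = 40 | m = 100 | m = 200 |
|---|---|---|---|
| 0.4 | 70% | 99.8% | >99.9% |
| 0.6 | 57% | 96% | 99.8% |
| 0.8 | 48% | 87% | 98% |
| 1.0 | 42% | 76% | 92% |

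For example, with m = 40 and s = 0.6 the median is 33.4, the standardised cut-off is −0.18, and the share is 57%. One mean fits a wide range of shares when it lies near the cut-off, and a much narrower range when it lies well above.

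**4. Is the proportion workable at the planned size?** With 96 per arm, the 95% interval half-width for a difference is at most 1.96 × √(2 × 0.5 × 0.5/96) = 0.141. Power for 60% v 80% (rates assumed, two-sided 5%): null SE √(2 × 0.7 × 0.3/96) = 0.0661, alternative SE √((0.24 + 0.16)/96) = 0.0645, and Φ[(0.20 − 1.960 × 0.0661)/0.0645] = Φ(1.09) = 86%. At alpha 0.05/3 (z = 2.394) it is Φ(0.645) = 74%. For 70% v 90% the two figures are 94% and 87%.

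**The case against.** The strongest reply is that nothing is lost. Ferritin is measured in each woman at entry and at Visit 5 in all three groups, so anyone can count those at or above 30, and the Statistical Analysis section allows for descriptive statistics. A reader might infer that the trial cannot say how many women leave hypoferritinemia; the documents do not support that. What stands is narrower: the count would be unplanned.

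A second reply is that continuous ferritin change answers the first research objective, which concerns the ferritin level, and that the article uses 30 ng/ml for diagnosis and entry without ever naming it as a treatment target. This is correct, and it is why the primary outcome should not be replaced. Nor does the article say that the primary analysis is of mean change. It says change; the mean is inferred from the t-tests and ANOVA, and rank methods are listed for non-normal data. Rank tests would limit the influence of a few very high values, although they do not yield a proportion either, and the Abstract ties them to symptoms.

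A third reply is that a condensed article may leave derived summaries to the full protocol or analysis plan. That would answer a bare request for a responder analysis. It does not answer the mismatch inside the article, where the sizing rests on a proportion that the fully stated outcomes leave out.

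Finally, the illustration depends on an assumed mean near the cut-off, and an SD reported beside the mean would separate its scenarios (at mean 40 they imply SDs from about 17 to 52 ng/ml). This is accepted. The range shows that the level does not settle the proportion; it does not predict the result.

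**Conclusion.** The point holds in a limited form. The proportion on which the trial was sized is neither a planned outcome nor covered by a listed test, and the planned ferritin outcome does not by itself determine it. This is worth correcting because it is cheap and lets the trial report the kind of effect its sample size assumed. It does not make the primary outcome invalid.

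The size of the gap depends on unknown data: 42% to 70% at or above 30 for an assumed mean of 40 and log SD from 1.0 to 0.4, narrowing to 76% to nearly 100% at a mean of 100. The reproduction of 96 per group rests on a relative reading of the 45% and on an assumed two-sided 5% level and 80% power.

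Ferritin at or above 30 is close to, but not the exact complement of, HWA prevalence. A woman who became anemic would leave HWA by definition while still below 30. The ferritin criterion does not count her as corrected.

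**What to change.** 1. Keep the primary outcome as it is.
2. Add to Secondary Outcome a supportive outcome: ferritin at or above 30 ng/ml at Visit 5 (yes/no), by allocated arm in all randomised women. Count women without a Visit 5 sample as not reaching 30, and give a complete-case sensitivity analysis, since loss may differ between arms.
3. Add to Statistical Analysis the risk difference with its 95% confidence interval. Report B v A first; treat A v C and B v C as descriptive, or adjust for multiplicity.
4. Reconcile Sample Size with Outcome Measures. State which outcome the 96 per group serves, what the 41.7% represents when every participant is below 30 at entry, and the alpha, sidedness and power. If the size is meant for ferritin change, recompute it on that scale.

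**Cost.** One extra analysis and a few sentences, with no new visit or sample. Dichotomising loses information, so the outcome stays secondary. Counting missing women as not reaching 30 dilutes the contrast slightly: with 5% lost in each arm, 60% v 80% becomes 57% v 76% (0.95 × 0.60 and 0.95 × 0.80). Adjusting all three contrasts would bring the power cost shown in step 4 of the working, which is the reason to name one contrast first.
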